### Data collection and management

Baseline data collection will be conducted through the electronic medical record (EMR) system of the participating centers. If certain variables are not recorded in the EMR, they will be collected retrospectively through telephone interviews. Table 2 presents the variables to be collected at baseline. A specialized secure database (CRF, case report form) will be established to facilitate the collection of standardized data from different centers. All data will be anonymized to ensure privacy, and each patient included in this study will be identified by an identity number. General variables (such as demographics, medical history, and medication history) and pregnancy- or puerperium-associated variables (including data on delivery and offspring-related variables) will also be collected for non-ASPP participants.

**Table 2 Tab2:** Baseline variables

• **Demographics**
▪ Age
▪ Ethnic: Han or other
• **General clinical variables**
▪ Date of admission and discharge
▪ BMI (calculated based on prepregnancy weight and height data)
▪ Previous or current smoking
▪ Previous or current drinking
▪ Previous or current drug abuse
▪ NIHSS and/or mRS at admission and discharge
▪ Blood routine index: RBC, WBC, PLT, etc.
▪ Blood biochemical index: TC, HDL-C, etc.
▪ Coagulation function index: TT, PT, FIB, APTT, etc.
▪ Other blood index: lupus anticoagulant, anticardiolipin antibodies, etc.
• **Medical history**
▪ Hypertension (if with record maximal SBP and DBP)
▪ Diabetes
▪ Migraine
▪ Polycystic kidney disease
▪ Cerebral vascular disease (if with record etiology)
▪ Myocardial infarction or angina
▪ Congestive heart failure
▪ Known atrial fibrillation or flutter
▪ Valvular heart disease
▪ Hypercholesterolemia
▪ Pulmonary embolism

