**Fig. 1 Fig1:**
[figure not shown]
The geographical distribution of centers participating in the ASPP study. The ASPP study aims to include 36 territorial or regional centers across 22 provinces in China

ASPP patients and non-ASPP participants from January 2015 to November 2024 will be included (Fig. 2). Table 1 lists the inclusion criteria and exclusion criteria. ASPP patients are defined as those who experience acute stroke events during pregnancy or within 6 weeks postpartum, confirmed by neuroimaging evidence of cerebral infarction or hemorrhage corresponding to their symptoms.

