▪ Neurologic: Intracerebral rebleeding (hemorrhagic stroke), vasospasm or delayed cerebral ischemia, intracerebral hemorrhage (ischemic stroke), brain herniation, etc.
▪ Systemic: Chest infection, urinary tract infection, deep venous thrombosis, pulmonary embolism, gastrointestinal bleeding, myocardial ischemia, etc.
• **Offspring-related variables**
▪ Term at birth: Pre-term, full-term, or post-term
▪ Gender
▪ Birth date
▪ Birth weight
▪ Apgar scores at 1, 5, and 10 min
▪ Transfer to NICU (if with record etiology)

*BMI* body-mass index, *NIHSS* National Institute of Health stroke scale, *mRS* modified Rankin Scale, *RBC* red blood cell, *WBC* white blood cell, *PLT* platelet, *TC* total cholesterol, *HDL-C* high-density lipoprotein cholesterol, *TT* thrombin time, *PT* prothrombin time, *FIB* fibrinogen, *APTT* activated partial thromboplastin time, *SBP* systolic blood pressure, *DBP* diastolic blood pressure, *AVM* arteriovenous malformation, *IA* intracerebral aneurysm, *CT* computed tomography, *CTA* computed tomography angiography, *MRI* magnetic resonance imaging, *MRA* magnetic resonance angiography, *DSA* digital subtraction angiography, *ECG* electrocardiography, *NICU* neonatal intensive care unit

^a^The first trimester is defined as the period from conception to 12 + 0 weeks of gestation. The second trimester spans from 12 + 1 weeks to 28 + 0 weeks of gestation. The third trimester begins after 28 + 1 weeks of gestation. Puerperium is defined as the period within 6 weeks postpartum

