#### Primary outcome

These are the following: For Aim 1, composite unfavorable outcome defined as *mRS* > 2 or EQ-5D index score < 0.7 at follow-up; for Aim 2, recurrent strokes confirmed by neuroimaging; and for Aim 3, the Apgar scores of newborns and results from Ages & Stages Questionnaires, Third Edition (ASQ-3) at follow-up.

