##### Assessment process

Assessors will document changes in patients’ functional status during follow-up, including self-reported and observed capabilities in activities of daily living, to accurately evaluate functional outcomes.

Neonatal asphyxia will be assessed using Apgar scores at 1, 5, and 10 min, with scores of 8–10 defined as no asphyxia, 4–7 as mild asphyxia, and 0–3 as severe asphyxia. The assessment will be conducted by healthcare personnel trained specifically in neonatal care to ensure the accuracy and consistency of the scores.

Developmental outcomes for offspring will be assessed using the Ages and Stages Questionnaire, Third Edition (ASQ-3), which is one of the most widely used tools for screening comprehensive developmental status in children aged 1 to 66 months. The ASQ-3 categorizes developmental status into five subdomains: (1) Communication, (2) gross motor, (3) fine motor, (4) problem-solving, and (5) personal-social. Based on scores in each subdomain, results will be classified as “above,” “close to,” or “below” the threshold. The assessment will be conducted by trained assessors to ensure the reliability and accuracy of the results [14].

Recurrent stroke and stroke during subsequent pregnancy are defined as events where women experience a recurrent stroke and a stroke during a subsequent pregnancy, respectively, both confirmed by corresponding medical or insurance records. Intrauterine death or stillbirth is defined as a dead fetus in the uterus at any trimester or the birth of a dead infant after 28 + 1 weeks of gestation. Critical illness is defined as the offspring requiring hospitalization due to a diagnosed disease, including neurological diseases (such as epilepsy and cerebral palsy), cardiovascular diseases (such as congenital heart disease), gastrointestinal diseases (such as necrotizing enterocolitis), respiratory diseases (such as allergic asthma), urological diseases (such as hypospadias), hematological and immunological diseases, and other major disorders.

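### The telephone fallback for data missing from the EMR does not exempt Apgar, so recalled scores could enter an Aim 3 primary outcome

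*Protocol article*

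**What the plan says.** **Role of Apgar.** The Primary outcome section names, "for Aim 3, the Apgar scores of newborns and results from Ages & Stages Questionnaires, Third Edition (ASQ-3) at follow-up". Table 3 sets neonatal asphyxia, assessed by Apgar, in bold. Its footnote defines the classes: 8–10 is no asphyxia, 4–7 mild and 0–3 severe.

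**Who assesses it.** Under Assessment process: "The assessment will be conducted by healthcare personnel trained specifically in neonatal care to ensure the accuracy and consistency of the scores".

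**Where the data come from.** Under Data collection and management: "Baseline data collection will be conducted through the electronic medical record (EMR) system of the participating centers". Then: "If certain variables are not recorded in the EMR, they will be collected retrospectively through telephone interviews". The same section says "Table 2 presents the variables to be collected at baseline", and Table 2 lists "Apgar scores at 1, 5, and 10 min" among the offspring-related variables.

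**Controls.** The same section states that "pregnancy- or puerperium-associated variables (including data on delivery and offspring-related variables) will also be collected for non-ASPP participants".

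**Timing.** "ASPP patients and non-ASPP participants from January 2015 to November 2024 will be included" (Participating centers and patient population). The first telephone round runs from December 2024 to February 2025 (Follow-up schedule).

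**The concern.** An Apgar score is set in the minutes after birth and written down there. If it is not in a participating center's record, the only substitute the article names is a telephone call. The mother, or whoever answers for her, would then supply three numerical scores from memory. The asphyxia classes turn on one point: an 8 remembered as a 7 moves a child from no asphyxia to mild asphyxia.

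Two things are at stake. The first is the accuracy of a primary outcome. The second is comparability. ASPP includes stroke up to six weeks postpartum, so a case may reach a participating center after delivering elsewhere, and that center may hold no birth record. If this happens more often in cases than in controls, one group's outcome rests more on memory than the other's. That can create or hide an association with neonatal asphyxia. The article does not ask for the source of each score to be recorded, so such an imbalance could not be seen afterwards.

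The comparison affected is with the pregnancy/postpartum non-stroke group. The nonpregnant stroke group has no index birth.

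**Working it through.** **Step 1: does the stated rule reach Apgar?**

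- The fallback follows directly on the baseline data source, and the baseline variables are those in Table 2.
- Apgar is in Table 2.
- No section exempts Apgar or any other primary outcome.
- Apgar is not among the key data whose absence excludes a participant (Table 1). A woman without an EMR Apgar therefore stays in the study, and the fallback can apply.

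**Step 2: how long is the recall?** Inclusion starts in January 2015. The date of the baseline calls is not given. If they coincide with the first follow-up round (December 2024 to February 2025), the longest interval is about 10 years.

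**Step 3: how large could the bias be?** The article gives no asphyxia rate, recall share or recall accuracy, so there is no stated figure to reproduce. Every rate below is an assumption. Only the 400 per group comes from the Abstract.

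Let p be the true asphyxia rate, equal in both groups, s the recalled share in cases, and se and sp the sensitivity and specificity of recall. Records are taken as error-free and controls as having no recalled scores. Then:

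- rate among recalled scores: q = p·se + (1 − p)(1 − sp)
- observed rate in cases: a = (1 − s)p + s·q
- spurious RR = a / p

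| se / sp | p | s | q | a | RR |
|---|---|---|---|---|---|
| 0.8 / 0.90 | 0.05 | 0.4 | 0.135 | 0.084 | 1.68 |
| 0.8 / 0.90 | 0.10 | 0.4 | 0.170 | 0.128 | 1.28 |
| 0.8 / 0.95 | 0.10 | 0.2 | 0.125 | 0.105 | 1.05 |
| 0.5 / 0.99 | 0.05 | 0.2 | 0.0345 | 0.0469 | 0.94 |
| 0.5 / 0.99 | 0.10 | 0.4 | 0.059 | 0.0836 | 0.84 |

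Over s = 0.2 to 0.4 and p = 0.05 to 0.10, over-reporting gives RR 1.05 to 1.68 and under-reporting gives 0.84 to 0.94.

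Expected z in the worst case, with pooled rate (0.050 + 0.084)/2 = 0.067:

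z = (0.084 − 0.050) / √(2 × 0.067 × 0.933 / 400) = 0.034 / 0.0177 = 1.92

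This is the expected z, not a ceiling on the observed one. With the unpooled standard error √[(0.050 × 0.950 + 0.084 × 0.916)/400] = 0.0176, a two-sided 5% test would reject with probability Φ[(0.034 − 1.96 × 0.0177)/0.0176], about 0.48.

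**Step 4: less extreme contrasts.** Here controls also have recalled scores, p is 0.05 or 0.10, and se/sp is 0.7/0.99, 0.7/0.95 or 0.9/0.95. The observed rate is built as in Step 3 in each group, with 400 per group.

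| Recalled share, cases vs controls | Spurious OR | Rejection rate (nominal 5%) |
|---|---|---|
| 20% vs 20% | 1.00 | 5.0% |
| 30% vs 10% | 0.95 to 1.17 | 5.1% to 8.1% |
| 50% vs 10% | 0.91 to 1.34 | 5.2% to 16.8% |

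With 320 per group (20% attrition), the last row's rejection rates are 5.2% to 14.4%. The bias can go either way and runs from negligible to material.

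**The case against.** **The two statements conflict.** A reader might infer this, since one section has trained staff assess Apgar and another allows recall by telephone. The documents do not support a strict contradiction. One statement can describe who scored the child at birth and the other how data are retrieved. What remains is that a recalled score does not carry the accuracy the first statement promises.

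**The fallback covers every Table 2 variable.** The text speaks only of certain variables. Table 2 also holds items no participant could report, such as APTT or anticardiolipin antibodies, so a sensible team might use the calls only for reportable items such as smoking. Multiple imputation is also planned for missing baseline data, so calls are not expected to fill every gap. This softens the point without removing it. Nothing says which variables are meant, and a mother can plausibly be asked about her child's Apgar.

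**The source does differ between cases and controls.** This too is an inference. The article does not say where either group delivered or how often Apgar is absent from the EMR, and the same rule applies to both. Controls may also deliver elsewhere.

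**The bias would be significant.** Giving both groups the 5% variance yields z = 0.034/√(2 × 0.05 × 0.95/400) = 2.2, but cases then have an observed rate of 8.4%, and the pooled test gives 1.92. That scenario also puts control recall at zero and counts 400 scored newborns per group, although Tables 2 and 3 allow for pregnancy termination and intrauterine death.

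**Recall bias is disclosed, and detail belongs in the full protocol.** The Discussion names recall and information bias in general terms and offers more centers as a remedy, which does not remove differential misclassification. A variable-by-variable source list may indeed sit elsewhere. The point here is narrower: the rule the article does state leaves a primary outcome open to recall.

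**Conclusion.** The point holds as a badly fixed data source for an Aim 3 primary outcome. The stated fallback can admit Apgar scores recalled up to about ten years after birth, and neither an exemption nor a record of source guards against it.

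That the error would differ between ASPP cases and pregnant/postpartum non-stroke controls is conditional on births outside the centers being more common in cases. Its size cannot be known from the article. The range of 0.84 to 1.68 for the spurious RR, with expected z at most about 1.9, rests on three assumptions: 20–40% recalled scores in cases and none in controls, true asphyxia of 5–10% in both groups, and the recall accuracies shown. With equal recall shares and equally accurate recall there is no spurious difference, though outcome accuracy still suffers.

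**What to change.** - **Data collection and management:** exempt Apgar from telephone recall in both groups. Take it from delivery or neonatal records. Where the participating center holds none, request the birth hospital's record where feasible; the Follow-up schedule already describes outside record requests for recurrent stroke.
- **Analysis:** base the primary Apgar analysis on recorded scores. Use any recalled scores only in a sensitivity analysis.
- **Reporting:** record the source of each score, and report source and missingness by group.
- **Assessment process:** reword the Apgar sentence to say *as recorded at delivery*.

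The cost is wording, one source field on the case report form, and record requests for births elsewhere. The real downside is that some Apgar values will be missing, possibly more often in cases. That would exchange part of a possible differential misclassification for differential missingness, which is why the by-group report and the sensitivity analysis belong to the fix.

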## Methods

### Design

This is a retrospective, observational, nationwide, multicenter study divided into three parts. The first part is a case-control study aimed at identifying the risk factors of ASPP and its prognostic predictors. The second part is a cohort study to evaluate the impact of ASPP on the risk of recurrent stroke. The third part is a cohort study to assess the impact of ASPP on the prognosis of their offspring.

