Grouping of non-ASPP participants is as follows:Non-ASPP participants include two matched control groups: The first group consists of participants in the pregnancy or postpartum period without a history of stroke (pregnancy/postpartum non-stroke group); the second group consists of nonpregnant or non-postpartum participants who have recently experienced a stroke (nonpregnant stroke group).Matching criteriaFor the pregnancy/postpartum non-stroke group, controls will be matched to ASPP cases in a 1:1 ratio based on age (±2 years) and hypertension history, with the latter stratified into preexisting hypertension, pregnancy-induced hypertension, or no hypertension.For the nonpregnant stroke group, a 1:1 matching strategy will be applied using age (±2 years), stroke etiology (classified by TOAST criteria), and preexisting hypertension status.Classification of pregnancy-related etiologies is as follows:Postpartum vascular diseasePregnancy-related hypercoagulable statesPregnancy-induced hypertensionPreeclampsiaAmniotic fluid embolismMatching of nonpregnant/postpartum patientsAge matching (±2 years)Matching based on stroke etiology, such as cardiogenic stroke, atherosclerotic stroke, small vessel disease stroke, and other identifiable causes (e.g., intracerebral hemorrhage)Health status and comorbidities, including common comorbidities such as cardiovascular disease, hypertension, and diabetesLifestyle factors, such as smoking and alcohol consumption historyDiscussion of the impact of pregnancy-related etiologiesEtiological characteristics, such as thrombosis resulting from pregnancy-related hypercoagulable states, hemodynamic changes caused by postpartum vascular disease, and hypertensive lesions associated with preeclampsiaPhysiological changes: Physiological changes during pregnancy, such as increased blood volume, blood pressure fluctuations, and alterations in coagulation mechanismsPsychological and social factors: Assessing the unique challenges faced by pregnant women in coping with stress, anxiety, and other mental health issues, as well as their potential impact on stroke occurrenceImpact assessment: When comparing ASPP patients with nonpregnant stroke patients, the influence of pregnancy-related etiologies on stroke recurrence rates and long-term prognosis will be clearly delineated.

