### Follow-up schedule

All participants will be followed up through telephone interviews. The initial follow-up is scheduled to take place between December 2024 and February 2025. The follow-up phase will consist of three rounds, each lasting 3 months and conducted every 3 years. The specific follow-up schedule is as follows:(1) First follow-up: Conducted between December 2024 and February 2025, focusing on stroke recurrence, cardiovascular health indicators, and quality-of-life assessments. During this period, any newly occurring stroke events will be documented, including the nature and severity of recurrent strokes, and changes in cardiovascular risk factors, such as blood pressure and lipid levels, will be monitored.(2) Second follow-up: Conducted between December 2027 and February 2028, continuing with telephone interviews and standardized questionnaires to assess participants’ life quality, including emotional state and daily activity capacity, while monitoring stroke and cardiovascular health status(3) Third follow-up: Conducted between December 2030 and February 2031 to further observe late-stage stroke and cardiovascular disease, particularly focusing on the increased cardiovascular risk phase post-menopause.

If participants report a stroke recurrence during the follow-up period, researchers will obtain the hospitalization records through the following process to confirm the event: First, researchers will contact the participant’s attending physician or the relevant hospital to systematically request the hospitalization records and medical information. Second, relevant medical records will be reviewed to verify the reported recurrence event, including confirmation of diagnosis, treatment course, and length of hospitalization. Additionally, if necessary, researchers will request neuroimaging assessments (such as CT or MRI) to further confirm the nature and severity of the stroke.

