### Statistical analysis

Descriptive statistics will express continuous variables as means (±standard deviation) or medians (interquartile range) and categorical variables as proportions. Chi-square tests or Fisher’s exact tests, along with Student’s *t*-tests or Wilcoxon rank-sum tests, will be used to compare demographics and clinical characteristics between cases and controls. Chi-square tests will compare dichotomous outcomes, while *t*-tests or Mann-Whitney *U*-tests will compare quantitative outcomes. Kaplan-Meier curves and log-rank tests will evaluate survival analyses, with Cox proportional hazard models calculating hazard ratios and 95% confidence intervals (CIs). Multivariate logistic regression will identify independent predictors, and linear or generalized linear models will assess the impact of ASPP and other factors on delivery outcomes and the ASQ-3 results. First, logistic regression will calculate odds ratios and 95% CIs for recurrent stroke. Subgroup analysis will evaluate potential differences in endpoints for predefined subgroups (such as gestational hypertension, preeclampsia, HELLP syndrome, gestational diabetes, trimester, and type of delivery). Multiple imputation will address missing baseline data, with a *p*-value of < 0.05 considered statistically significant.

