The findings of this study should be interpreted within the context of potential limitations. Firstly, this is a retrospective study, which is subject to several inherent biases, such as recall and information bias, potentially jeopardizing its validity. Secondly, follow-up via telephone interviews may lead to a high dropout rate. Thirdly, concerns among ASPP patients regarding the privacy of their offspring’s information may result in a significant number being unwilling to cooperate, leading to selection bias. To address these issues, expanding the sample size by including more centers would be an effective solution for achieving statistical validity. Finally, although this study focuses on the Chinese population and mainly includes the Han ethnic group as the primary ethnic cohort, it employs two methodological measures, geographical heterogeneity and biological consistency, to ensure the generalizability of the research findings. The study included 22 provinces representing different socio-economic and medical resource conditions to ensure geographical heterogeneity. According to previous national studies, in the Chinese population, the key risk factors for ASPP, such as hypertension and coagulation dysfunction, show minimal differences across different ethnic groups, suggesting that the study subjects have biological consistency [24, 25].

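### Telephone fill-in of baseline items missing from the medical record can bias Aim 1 odds ratios against women without stroke, and a larger sample does not cure it

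*Protocol article*

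**What the plan says.** All references are to the protocol article.

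- **Data collection and management.** Baseline data come from the centers' electronic medical records (EMR). For gaps: "If certain variables are not recorded in the EMR, they will be collected retrospectively through telephone interviews". No variable type is exempt. The same section has general variables, including medical and medication history, collected for the non-ASPP participants too. Table 2 lists smoking, drinking, drug abuse, migraine and oral contraceptive use.
- **Design.** "The first part is a case-control study aimed at identifying the risk factors of ASPP and its prognostic predictors".
- **Participating centers and patient population.** "ASPP patients and non-ASPP participants from January 2015 to November 2024 will be included". One control group consists of "participants in the pregnancy or postpartum period without a history of stroke", and for it "controls will be matched to ASPP cases in a 1:1 ratio", on age and hypertension history. The other control group has had a recent stroke outside pregnancy.
- **Follow-up schedule.** "The initial follow-up is scheduled to take place between December 2024 and February 2025". This is the earliest telephone contact that the article dates.
- **Statistical analysis.** "Multiple imputation will address missing baseline data", and p < 0.05 counts as significant.
- **Table 1.** Women lacking key baseline data (age, BMI, preexisting conditions, previous stroke, neuroimaging) are excluded.
- **Discussion, limitations.** The study is said to be open to "recall and information bias, potentially jeopardizing its validity". After listing this, dropout and unwillingness to cooperate, the authors propose enlarging the sample with more centers as the answer.

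**The concern.** A woman who had a stroke in pregnancy has had reason to go over her habits, headaches and medicines. A woman with an uneventful pregnancy years ago has not. If gaps in the record are filled by asking both, misclassification of the exposure can depend on case status, and the odds ratio can then move away from 1 for a factor that has no effect.

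Aim 1 is meant to name risk factors for pregnancy-related stroke, so a false lead on a lifestyle or medication item would appear as a finding. Because this is bias and not noise, the remedy named in the Discussion works the wrong way: more participants narrow the interval around the wrong value. If the source of each value is not kept, nobody can tell afterwards how much of an association rests on recall.

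**Working it through.** The article states no figure for recall error, so there is none to reproduce. The check covers the length of the gap, the possible size of the bias and the effect of sample size.

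**1. Length of the gap.** The earliest index date is 1 January 2015 and the first telephone round ends on 28 February 2025. That is 3,711 days, and 3,711 / 365.25 = 10.2 years. This is a maximum, and it assumes that baseline gaps are filled during that round.

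**2. Size of the bias.** None of these inputs is in the article; all are assumed:
- true odds ratio 1.0, so the same true prevalence p in both groups, with p = 0.10, 0.20, 0.30
- recall sensitivity Se = 0.90 in cases, 0.70 in controls
- specificity 0.98 in both groups
- share f of values obtained by telephone, equal in both groups
- EMR values without error

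Observed prevalence in a group = (1 − f)·p + f·[p·Se + (1 − p)·0.02].

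Example, p = 0.20 and f = 0.5:
- cases: 0.5·0.20 + 0.5·(0.180 + 0.016) = 0.198
- controls: 0.5·0.20 + 0.5·(0.140 + 0.016) = 0.178
- observed odds ratio: (0.198/0.802) / (0.178/0.822) = 1.14

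| Telephone share | p = 0.10 | p = 0.20 | p = 0.30 |
|---|---|---|---|
| 10% | 1.02 | 1.03 | 1.03 |
| 30% | 1.07 | 1.08 | 1.09 |
| 50% | 1.12 | 1.14 | 1.16 |
| 100% | 1.25 | 1.32 | 1.37 |

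Two variations:
- With equal sensitivity and equal shares, the observed prevalences are identical and the odds ratio stays at 1.0.
- With equal sensitivity (0.80) but unequal shares, 10% of case values and 50% of control values by telephone, the odds ratio is 1.01 to 1.09 at specificity 0.98 and 1.10 to 1.13 at specificity 1. So the share by group matters as well as the quality of recall.

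**3. Effect of a larger sample.** Take p = 0.20 and f = 0.5, with observed prevalences 0.198 and 0.178. For an unmatched two-sided test of two proportions at 5%, the probability of a significant result although the true odds ratio is 1.0 is:

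| Per group | Odds ratio | Probability of p < 0.05 |
|---|---|---|
| 400 (as planned) | 1.14 | 11.2% |
| 800 | 1.14 | 17.6% |
| 1,600 | 1.14 | 30.5% |

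The estimate does not move, and the false-positive rate rises.

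**4. Imputation in place of telephone values.** This can be biased too. Suppose case records are complete, and in controls the item is recorded for 80% of the exposed and 60% of the unexposed (assumed). The recorded control odds are then (0.80/0.60) times the true odds. Imputation under missing at random carries that forward, and a true odds ratio of 1.0 becomes 0.60/0.80 = 0.75, whatever the prevalence.

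**The case against.** Much of the case against stands.

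- **Recall bias is disclosed, and asking patients about gaps in the record is ordinary in retrospective work.** True. The remaining point is that the rule has no limit by variable type and that the remedy named cannot work.
- **A source flag and a sensitivity analysis belong in the case report form or analysis plan, which are not shown.** Fair. The article does not say that the two sources are pooled without a flag, and a reader should not infer it. The fill-in rule and the sample-size remedy, however, are stated in the article.
- **Imputation may simply come last: record, then telephone, then imputation of what is still missing.** That is a natural reading. The article gives no order among exclusion, telephone and imputation, but this does not show that two rules apply to the same value.
- **Few variables are affected.** Correct. Hypertension is a matching factor; missing BMI, preexisting conditions or previous stroke lead to exclusion; laboratory and imaging values are unlikely to be recalled; and the second control group also had a stroke.
- **The EMR is not a clean standard.** Also correct. A history taken at a stroke admission is taken after onset, so it can carry some of the same difference.

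A reader might go further and infer that relatives answer for women who died or are disabled, that stroke admissions record habits more fully than deliveries do, or that all baseline calls fall in 2024-2025. The document supports none of these as fact. Table 1 lets relatives agree and sign, and says nothing of their answering exposure questions. No figures on record completeness are given. The first telephone round lists recurrence, cardiovascular indicators and quality of life, not baseline exposures.

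**Conclusion.** The point holds as a design weakness of limited scope that is cheap to contain. The fill-in rule permits differential misclassification of a few history and lifestyle items in one contrast: ASPP cases against pregnant or puerperal women without stroke. Under the assumed recall accuracy the bias is negligible at a 10% telephone share (odds ratio 1.02 to 1.03), modest at half (1.12 to 1.16) and substantial only if nearly all values are recalled (1.25 to 1.37). Telephone share, recall accuracy and prevalence are all assumptions, so the document shows that bias is possible, not that it will be large.

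It is tempting to set these values against the 1.45 in the sample size section and conclude that bias could pass for the planned effect. That figure concerns high parity, which is not among the recall-prone items named here, so the comparison is not supported.

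One conclusion needs no assumed size: a larger sample does not reduce recall bias.

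**What to change.** 1. Record in the case report form, for each baseline value, whether it came from the EMR or by telephone, and report the telephone share by group.
2. For the recall-prone exposures, prespecify a paired Aim 1 analysis: one model with telephone values, and one with them set to missing and handled by the multiple imputation already planned.
3. Report an association as a risk factor without qualification only if it holds in both. Judge this on estimate and interval together, because the second model has fewer observed values.
4. Amend the limitations paragraph so that a larger sample is no longer offered as a remedy for recall bias.

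The cost is one extra field per variable, a second model run and some precision for poorly recorded items. The imputed model relies on missing at random and can itself mislead if recording depends on exposure (the 0.75 above), so it should accompany the telephone-inclusive model and not replace it. If calls have already begun, values whose source can still be traced should be tagged now.
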